## Abstract

**Background:**

Gestational diabetes mellitus (GDM) is one of the most common medical disorders in pregnancy. Evidence has demonstrated that moderate-intensity physical activity may reduce the risk of gestational diabetes. However, women at risk of GDM spend most of their time performing sedentary behaviors. Although researchers identified self-efficacy as a mediator to overcome physical activity barriers, exercise intervention during pregnancy based on self-efficacy theory has not been discussed so far. Furthermore, there is conflicting evidence regarding the effects of a physical exercise intervention on the incidence of GDM and other maternal or neonatal outcomes in women at higher risk for GDM.

**Methods/design:**

A single-center, parallel, randomized controlled trial will be conducted in a maternal–child health care center. A total of 244 pregnant women at high risk for GDM will be randomized into a study group receiving a self-efficacy-enhancing physical activity intervention or a control group receiving the usual care. The intervention will consist of four group sessions and everyday reminders by WeChat (Tencent, Shenzhen, China). The program will begin at approximately 13–14^+6^ gestational weeks and end at 36^+6^ gestational weeks. The primary outcomes will include the incidence of GDM, blood sugar values, and physical activity. The secondary outcomes will include physical activity self-efficacy, gestational weight gain, maternal outcomes, and neonatal outcomes.

**Discussion:**

The findings of this research will contribute toward understanding the effects of a self-efficacy theory-oriented physical activity program on the incidence of GDM, blood sugar values, physical activity level, gestational weight gain, physical activity self-efficacy, maternal outcomes, and neonatal outcomes.

**Trial registration:**

Chinese Clinical Trial Registry (CHiCTR) ChiCTR2200056355. Registered on February 4, 2022.

## Background

Gestational diabetes mellitus (GDM) is one of the most common medical disorders in pregnancy [1] and is associated with a greater risk of both short- and long-term adverse health outcomes for mothers and their offspring [2–6]. The prevalence of GDM is increasing worldwide, with an incidence rate of 16.7% documented in 2021 [7]. 14.8% of all women in mainland China were diagnosed with GDM in 2020 [8]. Well-recognized risk factors for GDM include higher maternal age, higher pre-pregnancy body mass index (BMI), family history of type 2 diabetes, polycystic ovary syndrome, hypothyroidism, previous macrosomia, ethnicity, certain lifestyle factors, and GDM or glucose intolerance in previous pregnancies [9–11]. Women with a combination of risk factors will have an even greater increased risk of GDM. Research has revealed that GDM reoccurs in nearly half of women with a history of GDM [12]. Thus, the best strategy to prevent GDM is to target the high-risk population [13].

Evidence has demonstrated that regular moderate-intensity physical activity (PA) may reduce the risk of gestational diabetes [14]. Furthermore, women with regular PA during pregnancy were more likely to give birth vaginally and less likely to have preeclampsia, gestational hypertension, excessive gestational weight gain, postpartum weight retention, or postpartum depression [14–17]. Thirteen clinical practice guidelines consistently recommend that all healthy pregnant women perform 150 min of moderate PA per week [18]. However, researchers have found that PA in women decreases from pre-pregnancy to pregnancy [19]. The majority of pregnant women do not meet the recommended amount of duration for daily PA [20]. Women at risk for GDM spend most of their time performing sedentary behaviors, despite a low prevalence of contraindications to exercise [21]. The prevalence of moderate and vigorous PA among obese pregnant women decreased from 4.8% in middle pregnancy to 3% in later pregnancy [22].

The factors related to PA in pregnant women include sociodemographic factors, pregnancy-related factors, objective environmental factors, physiological factors, psychological and cognitive factors, and social support [23–26]. Among these factors, the PA self-efficacy of pregnant women was identified as the key factor associated with insufficient PA [27, 28]. According to Bandura [29], self-efficacy refers to the belief in one’s capabilities to organize and execute the courses of action required to produce given attainments. A person with high self-efficacy is more willing to pursue an activity, despite difficulties, than a person with lower self-efficacy [30]. Researchers identified self-efficacy as a mediator to overcome PA barriers and increase PA [31, 32].

Dominant strategies to improve self-efficacy belief include direct successful experience, vicarious experiences, verbal persuasion, and emotional arousal [29]. Direct successful experience, including previous personal achievements and success, is the strongest influencing factor in self-efficacy. A vicarious experience can be defined as a person’s reinforcement of self-belief by watching a similar individual succeed in certain situations (i.e., “if they can do it, I can do it”). Verbal persuasion refers to guiding the individual to believe that they can succeed in specific situations through positive feedback and verbal clues. Emotional arousal refers to how an individual’s physiological state and their interpretation of that state can affect whether an experience is empowering or disempowering for them. To obtain a sense of self-efficacy, an individual can achieve a behavior successfully, observe others doing an assignment successfully, gain positive feedback about completing an assignment, or adjust their physiological and psychological status [30]. PA interventions based on self-efficacy theory have previously had a positive effect on PA among heart failure patients [33] and overweight and obese women [34].

Theory-based interventions guided by the constructs of theory have been found to have more effective and long-term effects than those without a theory as a basis [35]. Using theories also allows for structured planning, implementation, and evaluation of the intervention, which enhances the effectiveness of the program [36]. Although some theories have been used to promote PA during pregnancy [27], the effectiveness of self-efficacy-oriented PA intervention among women with high-risk factors for GDM remains understudied.

In mainland China, women are expected to be seen during pregnancy every 4 weeks until 28 weeks’ gestation, every 2 weeks until 36 weeks, and then weekly until giving birth. It is estimated that a woman “booking” at 6–13^+6^ weeks’ gestation and delivering at 40 weeks makes 11 antenatal care visits [37]. However, health education on PA is not covered by routine antenatal care. Furthermore, no strong evidence currently exists regarding the best intervention for the prevention of GDM. In addition, most PA interventions for pregnant women are designed for healthy pregnant women or overweight pregnant women rather than women with multiple risk factors [13]. The evidence on the effectiveness of PA interventions for women with high-risk factors for GDM is still inconclusive [38–41]. Moreover, most study participants in the work designing these interventions were Caucasian women, although Wang et al. [38] conducted a randomized control trial of overweight and obese pregnant women in Beijing where participants in the intervention group engaged in a hospital-supervised cycling program (3 times/week) for the period of 24 ± 2 weeks. Even though the incidence of GDM was lower in their intervention group, this result can be difficult to achieve on a large scale as it may take a lot of equipment, professionals, time, and money.

A pragmatic parallel, randomized controlled trial was designed to investigate the effect of a self-efficacy-enhancing PA intervention on the incidence of GDM, blood sugar values, and PA level. The secondary objectives of this study are to investigate the effect of the PA program on PA self-efficacy; gestational weight gain; maternal outcomes, such as gestational hypertension, preeclampsia, and mode of delivery; and neonatal outcomes, including gestational age at delivery, preterm birth, Apgar score, birth weight, birth length, macrosomia, low birth weight, fetal distress, amniotic fluid contamination, number of large for gestational age (LGA) infants, and number of small for gestational age (SGA) infants.

## Methods/design

### Study design

This is a parallel, randomized controlled clinical trial that will be conducted in Zhengzhou, China. Participants attending the antenatal clinic of the study hospital will be randomly allocated to a study group receiving a self-efficacy-enhancing PA intervention or a control group receiving the usual care. Baseline assessment will occur before 12^+6^ gestational weeks. Follow-up measurements will occur at 24–28 weeks, 35–37 weeks, and within 3 days after delivery. Table 1 summarizes the study design and timeline. This study is supported by a research grant (grant no. 72174216) from the National Natural Science Foundation of China.

**Table 1 Tab1:**
[figure not shown]
Study design and timeline

*Abbreviations*: *GDM* Gestational diabetes mellitus, *OGTT* Oral glucose tolerance test, *PA* Physical activity

The study protocol was designed using the Standard Protocol Items: Recommendations for Interventional Trials (SPIRIT) guidelines for interventional trials [42]. Any changes that need to be made to the trial protocol will be communicated to all investigators, the ethics committees, and the trial registry. The study has been approved by the Institutional Review Board of the School of Nursing at Sun Yat-sen University and by the study hospital.

### Eligibility criteria

Women who meet the following study inclusion criteria will be enrolled: (1) singleton pregnancy; (2) 5–12^+6^ weeks pregnancy; (3) ≥1 risk factor for GDM (e.g., maternal age ≥ 35 years old, pre-pregnancy BMI ≥ 24 kg/m^2^, family history of type 2 diabetes, polycystic ovary syndrome, previous macrosomia, previous GDM, previous glucose intolerance, previous fetal anomaly or hydramnion, current pregnancy with fetus growing greater than the gestational age, hydramnion, or repeated colitis).

Women will be excluded from this study if they have an exercise contraindication [18], such as severe cardiac or respiratory diseases, severe preeclampsia, uncontrolled hypertension, thyroid disease, type 1 diabetes, cervical insufficiency, persistent vaginal bleeding, threatened prematurity, placenta previa, ruptured membranes, poorly controlled anemia, fetal growth restriction, multiple pregnancies (≥ 3), bone or joint problems, severe obesity (body mass index > 35 kg/m^2^); are participating in other antenatal PA programs; or are currently being treated with metformin or corticosteroids.

### Sample size

The sample size of this study was calculated based on recent research available on the impact of PA on the incidence of GDM in Chinese overweight and obese pregnant women. Using information from that study [38] documenting incidence rates of GDM of 22% in the intervention group after PA intervention and 40.6% in the control group, we found that a sample size of a ≥ 98 women in each arm of this study will be required to detect a difference in the incidence of GDM between groups (80% power and *α* = 0.05). The treatment and control ratio is 1:1. Allowing for 20% attrition during pregnancy, ≥ 122 women in each arm will need to be recruited.

### Recruitment, setting, and informed consent

The present study will be undertaken in Zhengzhou, China, which is the capital of Henan Province and located in the central plains of China. Zhengzhou is a sub-provincial city and has a population of approximately 13 million people. The participants will be recruited from an antenatal clinic by researchers in a regional teaching hospital, which has > 6000 births annually. All pregnant women are required to visit the outpatient service to book into the hospital at their first clinical visit. Women will be recruited at the time of booking into the hospital at < 12^+6^ weeks’ gestation. The women who meet the eligibility criteria will be enrolled after they read and sign an informed consent form.

### Randomization and blinding

Pregnant women meeting the inclusion criteria and who agree to participate in our randomized controlled trial will be allocated randomly into either the intervention group or control group. Computer-generated randomization sequences will be provided by a biostatistician with no clinical involvement in the trial and stored securely on a password-protected computer. The randomization process will be done in blocks of four women. Each block will therefore result in the allocation of two women for the intervention and two women for the control group, ensuring a recruitment balance of 1:1 throughout the study.

Due to the nature of the intervention, it is not possible for study participants or the first researcher ([name]), who is delivering the intervention, to be blinded to the group allocations in this study. However, the other care providers, including nurses, midwives, doctors, and coaches, will be blinded to the group allocations. The first researcher ([name]) will assign women to the intervention or control group using a centralized, remote computer-generated randomizer called Sealed Envelope [43]. To minimize the risk of detection bias, every woman will be issued a unique three-digit study code. Therefore, the first researcher ([name]) will be blinded to the participant’s responses using the study code during data entry. Additionally, the first researcher ([name]) will be kept blinded to the group allocations during data analysis, and the statistician will analyze with the first researcher ([name]). All data, including both electronic and hard copies, will be destroyed 5 years after completion of the study.

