### Data management

The first researcher ([name]) will be responsible for monitoring the collection and quality of data as well as the participant recruitment and retention. All data collected will be kept strictly confidential, accessed only by members of the trial team, and stored on a secure computer with passwords. Each participant will be allocated an individual trial identification number.

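### A single published block size of four, with assignment made by the unblinded researcher who delivers the programme, lets anyone tracking the sequence foresee up to a third of allocations

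*Protocol article*

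**What the plan says.** All references are to the protocol article.

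- **Block structure (Randomization and blinding).** "The randomization process will be done in blocks of four women", and "Each block will therefore result in the allocation of two women for the intervention and two women for the control group". No other block size is given. The Sample size section agrees: "The treatment and control ratio is 1:1".
- **Who assigns (same section).** The first researcher "will assign women to the intervention or control group using a centralized, remote computer-generated randomizer called Sealed Envelope".
- **Blinding of that person (same section).** The section says it is not possible for the first researcher, "who is delivering the intervention, to be blinded to the group allocations in this study".
- **Oversight of recruitment (Data management).** The first researcher "will be responsible for monitoring the collection and quality of data as well as the participant recruitment and retention".
- **Who recruits (Recruitment, setting, and informed consent).** "The participants will be recruited from an antenatal clinic by researchers in a regional teaching hospital". These researchers are not identified further.
- **Safeguards (Randomization and blinding).** A biostatistician without a clinical role generates the sequence, it is stored under password, and a central remote system issues it. Allocation follows agreement to take part.

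The Abstract describes a single centre and 244 women. No stratification factor is mentioned, so the text implies one running sequence.

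**The concern.** Concealing the list is not the same as concealing the next assignment. With a known fixed block size, the allocations already made in a block narrow what can follow, and sometimes settle it. The person who makes the assignments has seen all previous ones, and the block size is in print.

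If someone with that knowledge can influence entry, women who are keener to exercise or at lower risk could be approached, encouraged or delayed according to the coming slot. The eligibility window (5 to 12+6 weeks) leaves room to shift the timing. The entry rule of at least one risk factor admits women of quite different underlying risk. Both GDM incidence and self-reported physical activity, which are primary outcomes, would be exposed.

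**Working it through.** The protocol gives no figure for predictability, so there is none to reproduce. Its total is consistent with the block design: 2 × 122 = 244 women, and 244 / 4 = 61 complete blocks. The point does not affect the sample size calculation.

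**Inputs.** Block of four, two per arm (Randomization and blinding); 244 women (Abstract). Assumptions: one unstratified sequence, women randomised one at a time, and an observer who knows the block size and all earlier allocations.

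**Step 1: certain assignments.** A 2:2 block has six equally likely orders: AABB, ABAB, ABBA, BAAB, BABA, BBAA. An assignment is certain when only one arm has places left.

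- Fourth place: certain in 6 of 6 orders.
- Third place: certain only when the first two women are in the same arm (AABB, BBAA), 2 of 6.
- First and second places: never certain.

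Expected certain places per block = 1 + 2/6 = 4/3. Share = (4/3)/4 = 33.3%. Over 61 blocks, 61 × 4/3 = 81.3, or about 81 of 244 women.

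**Step 2: best guess.** The observer guesses the arm with more places left, and tosses a coin when they are equal.

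| Place | Probability of a correct guess |
|---|---|
| 1 | 1/2 |
| 2 | 2/3 |
| 3 | (1/3 × 1) + (2/3 × 1/2) = 2/3 |
| 4 | 1 |

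Sum = 1/2 + 2/3 + 2/3 + 1 = 17/6. Rate = (17/6)/4 = 70.8%, against 50% with simple randomisation.

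**Step 3: alternatives.** Fixed blocks were enumerated exactly. Varying blocks were simulated (244 allocations, 300 runs), with an observer who knows the possible sizes but not their order.

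| Scheme | Certain | Best guess correct |
|---|---|---|
| Fixed 4 | 33.3% | 70.8% |
| Fixed 6 | 25.0% | 68.3% |
| Fixed 8 | 20.0% | 66.6% |
| Random 4, 6 | about 5% | about 69% |
| Random 4, 6, 8 | about 2% | about 68% |

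Random variation removes nearly all the certainty but little of the advantage in guessing.

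**Step 4: what it could do to the result (illustration only).** The protocol gives no figure for how far steering might go. Assume that women in the certain slots differ between arms in underlying GDM risk by 5, 10 or 20 percentage points and that other women do not differ. By symmetry a third of each arm is in such slots on average, so the arm difference shifts by 5/3 = 1.7, 10/3 = 3.3 or 20/3 = 6.7 points. The planned difference is 40.6 − 22 = 18.6 points.

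**The case against.** **The path to bias needs a fact that the protocol does not state.** A reader might infer that the first researcher recruits women and so can steer them. The documents do not support that. The recruitment section speaks only of researchers, and the Data management section gives the first researcher a monitoring task. Nothing says that this person screens, approaches or consents women. This objection stands and makes the point conditional. It does not remove the point, because nothing keeps this researcher apart from recruitment either.

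**The researcher does not hold the list.** This is correct, and it should not be read otherwise: the sequence is prepared independently and issued remotely. But deduction from past assignments does not require the list.

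**One third is the figure for an ideal observer.** It assumes one sequence, full tracking of block position, and each result known before the next woman is approached. The article does not say whether women are allocated singly or in batches. Intervention groups of 8–10 are formed after recruitment, and if several consented women were allocated together, fewer slots could be exploited. This stands, so a third should be read as an upper figure.

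**Consent already precedes allocation.** True, but a foreseeable slot can influence who is approached and when, before consent is sought.

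**Analysis could help.** It would go too far to say that no analysis can repair the damage. Baseline data are collected to compare the groups, and the PPAQ model adjusts for baseline and confounders. That can reveal and partly correct imbalance in measured factors. It cannot correct for unmeasured motivation, and the stated comparison for GDM incidence is a chi-squared test.

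**Conclusion.** The concern holds as a conditional weakness in allocation concealment. With one known block size of four, an observer with full knowledge of earlier allocations can foresee an expected third of assignments (about 81 of 244) and guess 70.8% correctly. The stated safeguards do not prevent this.

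The size rests on sequential allocation in a single unstratified sequence, and the absence of stratification is inferred from the article's silence. Selection bias would follow only if the first researcher, or someone told by that researcher, can affect whether or when a woman is approached or enrolled. A reader might conclude that the trial is biased or that 81 assignments were in fact known. The documents show neither. The change is worth making because it is cheap and closes a risk that later adjustment could correct only for measured factors.

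**What to change.** For all remaining randomisations:

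1. Have the biostatistician set randomly varying block sizes (for example 4, 6 and 8) in the remote system. Withhold the sizes from everyone who recruits, assigns or delivers the intervention, and remove the fixed size from operational documents.
2. Because varied blocks lower the guess rate only to about 68%, also separate the roles. State either that the first researcher does not approach, screen or consent women, or that an existing team member outside recruitment and delivery triggers the assignment.
3. State that an assignment is released only after baseline data have been entered. Consent already comes first, so only the baseline step is new.

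The cost is a setting in the existing randomiser, a few sentences, and a possible final imbalance of a few women between arms.

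The Trial status section expected recruitment, begun in February 2022, to finish by October 2022, so few or no randomisations may remain. If recruitment is complete, report who knew the block size and who enrolled women, and interpret the results with that limitation.

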### Intervention

Bandura’s self-efficacy theory [29, 30] guided the development of our self-efficacy-enhancing PA intervention to increase PA self-efficacy in women with high-risk factors for gestational diabetes mellitus; to decrease their incidence of GDM and blood sugar values; and to improve their PA level, proper gestational weight gain, maternal outcomes, and neonatal outcomes.

The intervention will start between 13 and 14^+6^ week’ gestation and will last for 24 weeks. After recruitment, about 8–10 pregnant women with similar expected dates of confinement will be included into a small group. The intervention will be conducted with the combination of face-to-face and online methods in small groups. The self-efficacy-enhancing intervention is complex.

The intervention includes the following components: (1) one 40-min face-to-face education session regarding GDM, healthy pregnancy weight gain, and PA during pregnancy conducted by an obstetric nurse and midwife; (2) one 50-min face-to-face exercise clinic visit conducted by a coach, obstetrician, nurse and midwife; (3) one 40-min daily exercise video including aerobic, resistance, and stretching exercises delivered to the women through WeChat platform (Tencent, Shenzhen, China); (4) daily reminders via the WeChat group to encourage the women to follow the 40-min video, performing the exercises and recording in their exercise diary; (5) one 40-min face-to-face education session regarding self-management of pregnancy-related symptoms conducted by an obstetric nurse and midwife; (6) one 40-min online education session regarding pregnancy-related emotion management conducted by an obstetric nurse, midwife and psychological consultant via Tencent Meeting (Tencent, Shenzhen, China); and (7) six offline and five online group discussion follow-up sessions (30–40 min for each session) every 2 weeks via Tencent Meeting or WeChat delivered by an obstetric nurse and midwife.

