The exercise video will be uploaded to the WeChat platform, a free application released in 2011 by Tencent. With its convenience and various services, including instant messaging, free phone calls, group discussion, sharing moments, mobile payment, small programs, and public accounts, WeChat has become the most prevalent social networking platform in China. The latest data from the 2020 Social Media User Behavior in China report indicates that 88.1% of WeChat users open their WeChat app every day, including 53.9% who do so for > 2 h per day [46]. We will advise the women to exercise at home following the exercise video for ≥ 5 days a week. Researchers will remind the women to exercise and record exercise diaries every day through the WeChat group.

An offline group discussion at the antenatal clinic of the study hospital or online group discussion via Tencent Meeting will be delivered by an obstetric nurse and midwife every 2 weeks. These sessions will aim to strengthen participants’ self-efficacy in PA and will be guided by a protocol. Pregnant women in small groups will sit around to discuss the problems that arise when doing exercise and share solutions on how to keep active with each other. Researchers will analyze the group members’ gestational weight gain and PA status in the prior 2 weeks. Feedback will be given to every group member. The nurse will provide encouragement and reinforcement of the participants’ efforts and successes and will empower them through support. Successful pregnant women will be invited to share their self-management strategies as role models. The duration of each group discussion session will vary from 30 to 40 min according to group members’ needs.

During 15–16^+6^ weeks’ gestation, face-to-face knowledge education about pregnancy-related symptom management will be provided by obstetric nurses and midwife at the antenatal clinic of the study hospital. After that, an offline group discussion will be held at the antenatal clinic of the study hospital. During 17–18^+6^ weeks’ gestation, online knowledge education about pregnancy-related emotion management will be offered by an obstetric nurse, midwife and psychological consultant online via Tencent Meeting. A group discussion will be held online after the knowledge education session by an obstetric nurse.

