	Providing positive feedback for the participant’s effort
Physiological states	Assessing and explaining the participant’s pregnancy-related symptoms and negative emotions
	Discussing strategies for managing symptoms, anxiety, or depression, such as positive self-talk and muscle relaxation

The intervention will be conducted by a multi-disciplinary team of obstetricians, nurses, midwives, psychological consultant, and coaches, all of whom have had >10 years of experience in their professional field. A 4-h training session will be provided to the team members by the first researcher ([name]) before the study begins. The study protocol will be reviewed and discussed to ensure consistency in delivering the PA intervention.

The Medical Research Council guidelines for the evaluation of complex interventions will be used to explore the process by which the intervention may have led to its effect or not [47]. Multiple methods of data collection will be used to assess the implementation of the intervention, the mechanisms of impact, and context effects (Table 3).

**Table 3 Tab3:** Process evaluation items, indicators, and methods of measurement

Process evaluation items		Indicators	Measurement

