### Control group

Participants in the control group will receive the customary regular consultations with the midwife, nurse, or obstetrician. They will not be discouraged from exercising on their own. Neither group will receive special recommendations about diet or other standard antenatal care delivered through prenatal health education.

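### The professions named as blinded to allocation also deliver the intervention, and the first researcher's blinding at analysis is not credible

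*Protocol article*

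**What the plan says.** The section Randomization and blinding of the protocol article makes three separate statements.

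- Participants and the first researcher, who delivers the intervention, cannot be blinded, but "the other care providers, including nurses, midwives, doctors, and coaches, will be blinded to the group allocations".
- To limit detection bias, each woman receives a three-digit study code. The code is said to keep the first researcher from knowing whose responses are being entered.
- At the analysis stage, the first researcher "will be kept blinded to the group allocations during data analysis, and the statistician will analyze with the first researcher".

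The Intervention section describes delivery: "The intervention will be conducted by a multi-disciplinary team of obstetricians, nurses, midwives, psychological consultant, and coaches". Its components include "one 40-min face-to-face education session regarding GDM, healthy pregnancy weight gain, and PA during pregnancy conducted by an obstetric nurse and midwife" and "one 50-min face-to-face exercise clinic visit conducted by a coach, obstetrician, nurse and midwife". The group discussions "will be delivered by an obstetric nurse and midwife every 2 weeks"; there are six offline and five online, 11 in all.

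Under Control group, control women receive "customary regular consultations with the midwife, nurse, or obstetrician". No coach is mentioned there. Under Data management, the first researcher also monitors data collection, data quality, recruitment and retention.

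**The concern.** A person who leads a session attended only by intervention women knows that those women are in the intervention arm. If the professions called blinded are the ones leading the sessions, the protocol claims a design property that the trial does not have for those staff. The claim about the first researcher raises the same problem at a later stage: someone who assigned the women and worked with the intervention arm is said to be unaware of allocation when the data are analysed.

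Two things are at stake. First, analysis decisions could be influenced by someone who knows the arms. The mixed-effects model for the activity score, for example, adjusts for confounders chosen in a preliminary step. Second, outcomes that rest on clinical judgement could be recorded by staff who know the arm. Secondary outcomes matter here because the Discussion says that a benefit in any primary or secondary outcome should lead to the programme being considered for regular care. A trial report that repeated the blinding statement would overstate the protection against bias.

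**Working it through.** The point involves no calculation, and no design figure depends on it: the sample size rests on the two GDM rates, power, alpha and attrition. The check sets the passages side by side.

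**Step 1. Providers called blinded against providers who deliver.**

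| Profession listed as blinded | Role in the Intervention section | Role in control care |
|---|---|---|
| Nurses | Education sessions, exercise clinic visit, all 11 discussions | Usual consultations |
| Midwives | Education sessions, exercise clinic visit, all 11 discussions | Usual consultations |
| Doctors (obstetricians) | Exercise clinic visit | Usual consultations |
| Coaches | Exercise clinic visit | None stated |

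All four listed professions deliver at least one face-to-face component. Coaches and obstetricians are not named for the discussions, which fall to a nurse and a midwife.

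**Step 2. The first researcher's roles.** This person assigns women using the remote randomizer, is described as delivering the intervention, trains the delivery team (Intervention section), monitors data collection and retention (Data management), and then analyses jointly with the statistician. Knowledge gained in the first two roles is not lost by the last. The article gives no mechanism for blinding at analysis. The study code does not supply one: the article claims only that it masks responses at data entry, which is a different thing from masking allocation.

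**Step 3. Which outcomes are exposed.**

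- *OGTT glucose and GDM (primary).* Taken from the medical database and judged against fixed cut-offs, so little affected by who knows the arm.
- *Physical activity (primary).* Self-reported on the PPAQ by women whom the article already declares unblinded. Correcting the statement on providers does not change that.
- *Maternal and neonatal outcomes (secondary).* The article defines 5 maternal and 11 neonatal outcomes, 5 + 11 = 16. At least 5 of the 16 involve clinical judgement: mode of delivery, postpartum blood loss, Apgar score, fetal distress and meconium staining. This counts outcomes that involve judgement. It does not count outcomes shown to be recorded by staff who know the arm.
- *Gestational weight gain (secondary).* Weight is read from a calibrated electronic scale to 0.1 kg, which leaves little room for judgement.

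**Step 4. Who records the delivery outcomes.** They come from medical records. The article does not say whether session staff attend births or write those records.

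**The case against.** The strongest defence is that the other care providers are routine antenatal and ward staff outside the session team. The team is a defined group that receives a 4-hour training, and the hospital has more than 6000 births a year, so many clinicians could be unaware of the arm. This stands in part: staff outside the team may well be blind in practice. It does not rescue the sentence as written. The article draws no line between the two groups, control care is given by the same professions, and the offline sessions take place in the hospital's own antenatal clinic. The defence fails outright for coaches, who appear only in the intervention.

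A second defence is that masked group labels could protect the joint analysis. They could help, and a statistician working alone on coded arms would gain real protection. The article does not describe such labels, and they would protect less with a co-analyst who assigned the women and delivered the intervention.

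A reader might go further and infer that the trial has no protection against detection bias at all. The documents do not support that. The article ties detection bias to the study code rather than to provider blinding, coded data entry may give some protection, and the glucose outcomes are laboratory values. A reader might also infer that delivery outcomes will be judged by session staff. Nothing in the article says so; it remains a possibility.

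**Conclusion.** The concern holds as an internal contradiction together with one claim that cannot be believed. Staff who deliver sessions know who is in the intervention arm, although all four of their professions are described as blinded. The first researcher cannot credibly be blind at an analysis carried out jointly with the statistician.

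The size of any resulting bias cannot be derived from the article, and no sample size figure changes. The effect on OGTT glucose and GDM is small, and the self-report problem for physical activity exists regardless. What remains is exposure in analysis choices, and possibly in clinician-judged secondary outcomes. The second part rests on an assumption that the article neither confirms nor excludes: that some staff who know the arm record those outcomes.

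**What to change.** 1. Reconcile Randomization and blinding with Intervention. Describe participants, the first researcher and everyone who delivers a session as unblinded. Limit any claim of provider blinding to staff outside the session team.
2. State that clinician-judged outcomes will be interpreted as potentially open-label, and distinguish them from laboratory glucose.
3. Withdraw the statement that the first researcher is blinded at analysis. Have the trial statistician run and freeze the first primary analysis on arms coded A and B, with the first researcher joining only afterwards.
4. Have someone other than the analyst hold the arm key and the randomization sequence. The article mentions a biostatistician who supplies the sequences and, separately, a statistician who analyses, without saying whether they are the same person. If they are, the two tasks need to be separated.

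The cost is a change of wording and a reassigned analysis task. A further person is needed only if one individual now holds both the sequence and the analysis.
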